#### Blinding

All participants will be partially blinded to group assignment as they will not be told which study group will yield greater benefits as both groups receive supervised PA. The research co-ordinator will be responsible for scheduling all data collection assessments with research assistants (RAs) who are blind to group allocation. An independent group of RAs (separate than those who are engaged in data collection) will conduct the behavioral counseling and group webinars.

#### Sample size

The power calculation, based on a mixed model test with two intervention levels (i.e., PA + BC and PA + EC) and one dependent variable (i.e., MVPA), was performed in G*Power [48] to estimate the sample size to detect the global effect of treatments on outcomes. Based on our pilot trials [32, 49] and benchmarks for PA interventions in people LWBC [50], the total sample size of 196 will provide 80% power with alpha 0.05 to detect a difference of 24 min per day of MVPA between the groups based on pilot data [32]. Attrition rates are expected to be 20% [51], and thus the target sample size will be 236 (i.e., 118 in the PA + BC group and 118 in the PA + EC control group) to detect meaningful differences in MVPA. Equal representation of males, females, and other gender identities will be recruited to ensure sufficient power for sex and gender analyses.

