#### Participant recruitment

A total of 236 participants (*n* = 118 in each study group) will be recruited through listservs and flyers distributed in the community and posted in local cancer organizations. Recruitment will be performed through word of mouth and advertisements both online and through local community cancer support centers.

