#### Randomization

Participants will be 1:1 randomized to either the PA + EC or the PA + BC group. Randomization will be performed using a stratified randomization scheme in the REDCap Randomization Module after baseline assessments. The sequence will be random permuted blocks of varying sizes, stratified by prior chemotherapy (yes versus no), age (< 65 versus ≥ 65 years), and sex (female versus male) to balance treatment characteristics that would potentially impact the severity of fatigue and intervention response [46]. Randomization codes will be kept in a pre-made digital file that is separate from other study records. Only the research co-ordinator will have access to the randomization codes. Following randomization, the research co-ordinator will update the randomization log to indicate the code has been used and include the ID number of the participant it was assigned to.

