#### Statistical analysis

A series of multilevel models using full information maximum likelihood to examine changes in the primary (i.e., MVPA) and secondary outcomes (i.e., reflective, regulatory, and reflexive processes from the M-PAC, physical function, QoL) will be conducted at the four time points. Multilevel modelling allows for simultaneous assessments of within person variations at each time measurement (level 1), which will be nested within study group (level 2). Finally, study group will be nested within study site (level 3). Although our primary time point of T2 will confirm the adherence reported post-intervention, inclusion of the T3 and T4 assessments allows us to determine if adherence is maintained. Fixed effects included in models will be time (i.e., baseline, T1, T2, T3, and T4), group (i.e., PA + BC intervention and PA + EC attention control), and interaction. All models will be estimated while adjusting for covariates (e.g., baseline PA, age, sex, treatment and cancer type). We will use the same analytical approach to assess differences across subgroups (e.g., sex, gender, drop-outs) by modeling the changes over time. Differences between men and women will be analyzed by adding a gender indicator variable to each of the models. The gender covariate will be crossed with the model’s independent variable so their interaction will be in the model. An intention-to-treat analysis will be used. For missing data at post-intervention or follow-up, all available data will be included under the missing-at-random assumption of the mixed-model analysis. Additionally, sensitivity analyses will be conducted to evaluate the robustness of our findings under alternative missing data assumptions, such as not-missing-at-random. The PROCESS macro for SPSS [77] will be used to examine mediation effects of the reflective, regulatory, and reflexive processes between groups (PA + BC group; PA + EC group) and MVPA and indirect effects across the path model. Cost and QALY differences between groups will be calculated using ordinary least squares regression analyses. Incremental cost-effectiveness ratios (ICER) will be calculated by dividing the adjusted incremental costs by incremental effects. ICER uncertainty will be measured by bootstrapping using at least 5000 replications.

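### The recruitment target of 236 allows for about 16.9% attrition, not the stated 20%: 196 was multiplied by 1.2 instead of divided by 0.8 (minor arithmetic error)

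*Protocol article*

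**What the plan says.** The Sample size section of the protocol article gives three linked figures. The first is the number required: "the total sample size of 196 will provide 80% power with alpha 0.05". The other two are the expected loss and the target drawn from it: "Attrition rates are expected to be 20% [51], and thus the target sample size will be 236". The target is split into 118 per arm.

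The Participant recruitment section uses the same figure as the number entering the trial: "A total of 236 participants (*n* = 118 in each study group) will be recruited". The Abstract also gives 118 per group. The Randomization section sets equal allocation: "Participants will be 1:1 randomized to either the PA + EC or the PA + BC group".

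So 196 is the number wanted after losses, and 236 is the number recruited before them. The Sample size section does not say by which assessment the 20% is expected to be reached. The Statistical analysis section names T2 (post-intervention) as the primary time point. For participants with missing visits it says that "all available data will be included under the missing-at-random assumption of the mixed-model analysis".

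**The concern.** The protocol presents the target as the consequence of the required number and the attrition rate. Anyone who removes 20% from 236 gets fewer than 196. The three figures therefore cannot all hold, and nothing elsewhere in the article reconciles them.

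At stake is a stated design figure for the primary outcome. A reader who relies on this section will believe that 20% loss is fully covered, when the target covers somewhat less. The same figure would also be the reference for judging retention: losses between 16.9% and 20% would appear to be within plan, although the protocol's own required number had already been missed.

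**Working it through.** **Inputs**, all from the protocol article:
- Required total N = 196, power 80%, alpha 0.05 (Sample size). Sidedness is not stated; two-sided is assumed, and one-sided is also shown.
- Attrition d = 0.20 (Sample size).
- Target = 236, or 118 per arm (Sample size; Participant recruitment).
- Allocation 1:1 (Randomization).

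**Step 1. Reproduce the stated target.**
N × (1 + d) = 196 × 1.20 = 235.2, rounded up to 236. This matches the protocol exactly.

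**Step 2. Apply the attrition rate to those enrolled.**
N / (1 − d) = 196 / 0.80 = 245. With equal arms this becomes 246, or 123 per arm. The stated 236 is 9 short of 245 and 10 short of 246, too many to be rounding.

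**Step 3. What 236 leaves at 20% attrition.**
236 × 0.80 = 188.8, about 189. The shortfall is 196 − 189 = 7 participants (7.2 / 196 = 3.7%).

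**Step 4. The attrition that 236 can absorb.**
1 − 196 / 236 = 40 / 236 = 16.9%.

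**Step 5. Effect on power, completers only.**
The protocol gives no SD, within-person correlation or standardised effect, so 196 cannot be rebuilt. I take its 80% at 196 as true and scale from there, using a two-group comparison of means as a stand-in for the mixed-model test.
- Implied standardised effect at 98 per arm: (1.960 + 0.842) / √(98/2) = 2.802 / 7 = 0.400.
- Power at 188.8 / 2 = 94.4 per arm: Φ(0.400 × √(94.4/2) − 1.960) = Φ(2.750 − 1.960) = Φ(0.790) = 78.5%.
- A noncentral-t calculation, with implied effect 0.402, also gives 78.5%. One-sided alpha gives 78.7%.

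**Step 6. Effect on the detectable difference.**
At fixed power this scales with 1/√N: 24 × √(196 / 188.8) = 24 × 1.019 = 24.5, in the protocol's own unit, against 24.0.

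| Quantity | Protocol | Recomputed |
|---|---|---|
| Target for 196 after 20% loss | 236 | 245 (246 for equal arms) |
| Left from 236 at 20% loss | 196 (implied) | about 189 |
| Attrition that 236 absorbs | 20% | 16.9% |
| Power at 20% loss, completers only | 80% | about 78.5% |

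**The case against.** The strongest case on the other side concerns the consequence. A reader might infer that the trial fails to deliver its 80% power. The document does not support that, for three reasons.

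1. The 78.5% treats every participant who drops out as contributing nothing. The Statistical analysis section plans a multilevel model with full information maximum likelihood over five assessments, so someone lost after T1 still adds information.
2. The timing of the 20% is not given. If some of it falls after T2, fewer than 20% are missing at the primary time point. The article does not allow an assumption either way.
3. The base figure is unverified. The Sample size section says the calculation "was performed in G*Power [48] to estimate the sample size to detect the global effect of treatments on outcomes" but reports too little to rebuild 196, and the percentage here comes from a simpler two-group comparison.

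All three stand as limits on the size of the effect. As a rough gauge, 236 − 188.8 = 47.2 participants would be lost, and the shortfall is 7.2. Partial data worth 7.2 / 47.2, about 15% of a full participant per dropout, would close the gap. The article gives no figures to say whether that would be reached.

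None of this rescues the arithmetic. The 196 is itself described as resting on a mixed-model test, and the protocol then adds an allowance that counts dropouts as lost. On that logic the allowance is too small.

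Nor is this a detail left to a fuller document. The article states all three figures and the inference between them, and no further detail would make 80% of 236 equal 196.

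**Conclusion.** The concern holds as a minor arithmetic error in a stated design figure. The target of 236 covers attrition of at most 16.9%, not the 20% expected, because 196 was multiplied by 1.2 instead of divided by 0.8. These figures need no assumption beyond the protocol's own numbers.

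The power consequence is conditional. If 196 gives exactly 80% power, and if dropouts contribute nothing, power at 20% attrition is about 78.5%, a loss of about 1.5 percentage points. The planned analysis may recover part of that. The finding does not show that the trial is materially underpowered, and it calls for no change to randomization or analysis.

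**What to change.** Keep the target at 236 and restate the attrition sentence in the Sample size section in one of two ways:

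- *80% power holds if attrition does not exceed about 17%.* This is the safer wording, since it needs no power model beyond the protocol's own claim for 196.
- *With 20% attrition about 189 participants remain, giving approximately 78.5% power on a completers-only basis.* The qualifier should stay, because the percentage depends on it.

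Either version costs one sentence and no extra participants; a stated figure becomes slightly less favourable. Recruitment numbers in the Abstract and the Participant recruitment section stay as they are. If the sponsor would rather keep both the 20% and the 80%, the consistent target is 246 (123 per arm). That means 10 more participants and matching edits in those two places, which is hard to justify for a difference this small.

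### The sample size section promises sufficient power for the sex and gender analyses, but N = 196 was sized only for the overall two-arm effect, and the gender categories recruited and modelled do not match

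*Protocol article*

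**What the plan says.** The Sample size section of the protocol article describes a mixed-model power calculation with two intervention levels and one outcome (MVPA), run "to estimate the sample size to detect the global effect of treatments on outcomes". Its result is that "the total sample size of 196 will provide 80% power with alpha 0.05". The planned between-arm difference in MVPA is given as 24 min/day. The recruitment target is then raised to 236 for 20% attrition. The paragraph ends: "Equal representation of males, females, and other gender identities will be recruited to ensure sufficient power for sex and gender analyses".

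The Statistical analysis section says: "Differences between men and women will be analyzed by adding a gender indicator variable to each of the models". It then crosses that gender term with the model's independent variable, so that an interaction is fitted. The Randomization section stratifies by sex at two levels, female and male. The Background makes moderation of treatment efficacy a secondary objective and lists sex and gender differences in activity maintenance among three gaps that the trial will address. The Secondary outcomes section says that all outcomes will be broken down by gender and sex, and it plans two-step gender questions and a Gender Index.

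**The concern.** Equal category sizes give the best interaction power available at a fixed total, but they do not make that power adequate. The total here was fixed by the two-arm comparison alone, and an interaction between treatment and a subgroup is estimated much less precisely than the treatment effect itself. The article supplies no effect size, variance or calculation for the sex and gender analyses, yet it asserts that their power is sufficient.

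The risk lies in interpretation. With sufficient power on the published record, a non-significant interaction invites the conclusion that the intervention works equally well across genders, when the trial may have had little chance of showing otherwise. The Secondary outcomes section expects this work to prompt gender-specific care pathways, so the distinction matters.

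There is also an inconsistency. The power sentence rests on equal recruitment of three categories, but the model that is meant to use that power compares two.

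**Working it through.** **Inputs.** From the Sample size section: 196 evaluable, 80% power, alpha 0.05, difference of 24 min/day, target 236, attrition 20%. From Randomization: 1:1 allocation. Assumptions: two-sided test with one degree of freedom (the article does not state sidedness); the same variance and within-person correlation in every subgroup; and the independent variable crossed with gender is read as study group.

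**The plan's own figure.** No SD or repeated-measures correlation is given, so 196 cannot be rebuilt from stated inputs. Solving backwards as a two-group comparison with 98 per arm:
- d = (1.96 + 0.84)/√(98/2) = 2.80/7 = 0.40, which implies an SD of about 24/0.40 = 60 min/day.
- Check: d = 0.40 with 98 per arm gives power 0.7996, and the usual formula asks for 99 per arm (198 in total). The figure is consistent with this reading.

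The steps below need only the ratio of effect to standard error, which 80% power fixes at 2.80. They do not depend on the unstated SD.

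**Standard errors** (σ = SD, N = total, arms equal):
- Main effect: variance 4σ²/N.
- Treatment effect within one half: 8σ²/N. Within one third: 12σ²/N.
- Difference between the effects in two halves: 16σ²/N, so the SE is √(16/4) = 2 times that of the main effect.
- Difference between the effects in two of three thirds: 24σ²/N, so the SE is √(24/4) = √6 = 2.45 times that of the main effect.

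**Interaction power at N = 196.** Let k be the interaction as a multiple of the planned main effect. Power = Φ(c − 1.96) + Φ(−c − 1.96), with c = 2.80k/2 for halves or 2.80k/2.45 for a pair of thirds.

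| k | Two equal categories | Pair among three equal categories |
|---|---|---|
| 0.5 | 10.8% | 8.8% |
| 1 | 28.8% | 20.8% |
| 1.5 | 55.6% | 40.4% |
| 2 | 80.0% | 62.8% |

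For example, k = 1 with halves gives c = 1.40 and Φ(−0.56) ≈ 0.288. A two-degree-of-freedom test across three categories at k = 1 gives 16.1% (evenly spaced effects) to 20.1% (one category differs).

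**Interaction needed for 80% power.** 2.0 times the main effect with halves (2 × 24 = 48 min/day), or 2.45 times for a pair of thirds (2.45 × 24 ≈ 59 min/day).

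**Sensitivity at k = 1.**
- All 236 retained: 33.6% (halves), 24.1% (pair of thirds).
- 236 × 0.8 ≈ 189 retained: 28.0% and 20.2%.
- One-sided throughout, the ratio becomes 1.645 + 0.842 = 2.49. Then Φ(2.49/2 − 1.645) ≈ 34% and Φ(2.49/2.45 − 1.645) ≈ 26%.

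**Other sex and gender analyses at N = 196.**
- Treatment effect within one half: c = 2.80/√2 = 1.98, power 50.8%. Within one third: c = 2.80/√3 = 1.62, power 36.6%.
- Plain contrast between men and women of the planned standardized size, ignoring treatment: 80% with halves. With thirds, c = 2.80 × √(2/3) = 2.29, power 62.8%.

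**Categories side by side.** Sample size: three equal groups, 236/3 ≈ 79 recruited or 196/3 ≈ 65 evaluable each. Statistical analysis: one indicator, men versus women. Randomization: two-level sex. Under the described model, about a third of the intended sample has no stated place in the gender contrast.

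**The case against.** The strongest reply is that the power figures depend on an interaction size that the article never states. That stands, and it is why a range is shown. A reader might infer that the plan simply has 20–30% power for these analyses, but that holds only if the interaction equals the whole main effect. At twice the main effect, two equal categories do reach 80%.

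A second reply is that not every sex or gender analysis is a treatment interaction. The Background's wording on differences in maintenance can be read as a plain gender or gender-by-time difference, and a plain contrast could reach about 80% with halves. This also stands, so it would be wrong to say that balance cannot give adequate power for any planned gender analysis. It does not rescue the sentence as written: the three-way equality lowers that figure to 63%, and the model adds the interaction.

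Three stronger readings are tempting but not supported:
- That equal recruitment is unachievable because no quota or enrolment rule is given. A journal article commonly leaves such mechanics to the full protocol.
- That drop-outs will be used as a treatment-effect moderator. The text says only that the same approach will "assess differences across subgroups (e.g., sex, gender, drop-outs) by modeling the changes over time". It does not call drop-out a moderator or say that a treatment effect will be estimated conditional on it, and drop-out is not defined as having no later data. A descriptive comparison is an ordinary reading.
- That the third category is excluded from all analysis. The Secondary outcomes section plans breakdowns by gender and sex and a Gender Index. The mismatch concerns the model described under Statistical analysis.

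**Conclusion.** The point holds in limited form. The article claims a power property that its own calculation does not establish. For the treatment-by-gender interaction, the claim is true only if the interaction is at least about 2 times (two equal categories) or 2.4 times (a pair among three) the effect for which the trial was sized. An interaction as large as the entire planned effect would be missed about 70–80% of the time. Unequal categories would lower power further.

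This rests on a two-sided single-degree-of-freedom test, equal variance across subgroups, and reading the crossed variable as study group. Sidedness and the number retained move the figures by a few percentage points and do not alter the conclusion. The mismatch between three recruited categories and a two-category model needs no assumption. Stratifying by two-level sex is not itself an error, since sex and gender are separate variables, but it does not secure balance between arms in the third category. These are secondary analyses, and the primary comparison is unaffected.

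**What to change.** 1. In Sample size, withdraw the statement that equal representation ensures sufficient power. The representation goal can stay as a recruitment aim.
2. Label the treatment-by-sex and treatment-by-gender analyses exploratory. Report estimates with confidence intervals, and state the interaction detectable with 80% power: about 2 times the main effect for two equal categories and about 2.4 times for a pair among three.
3. Reconcile Sample size with Statistical analysis, so that every recruited category has a defined place in the model and it is clear which analyses use sex and which use gender.

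If the sponsor prefers to keep a power claim, the interaction size behind it must be stated. For an interaction equal to the main effect, 80% power would need about 4 × 196 = 784 evaluable participants with two equal categories, or 6 × 196 = 1,176 for a pair among three.

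Cost: a favourable claim is withdrawn, and the gender term in the model has to be settled before analysis. The sample size, recruitment and assessments do not change.

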#### Study groups

The goal of both groups is to gradually increase PA to a minimum of 90 min of MVPA per week following the updated ACSM PA guidelines for people LWBC [46]. People LWBC in both groups will be given an individualized, home-based aerobic and resistance prescription based on baseline assessment and previous work (Table 2) [32, 49]. The duration and intensity will account for the participant’s baseline physical function results, PA history, and preferences. The prescribed intensity will be 40–59% of the maximum heart rate reserve (i.e., moderate intensity) for weeks 1–6 and 60–70% (i.e., moderate to vigorous) by the end of the intervention. Initial PA duration will also be individualized but generally begin at 10–20 min per session, gradually increasing aerobic duration by 5 min each subsequent week. An aerobic duration of 30 min will be achieved by and maintained after week 6 of the intervention to meet PA guidelines [52]. Following aerobic PA, a standard progressive, resistance training program with resistance bands provided to each participant for two or three sets of 8–12 repetitions each at an intensity of 12–15 on a rating of perceived exertion (RPE; 6–20) scale (approximately 60–80% of one-repetition maximum). The resistance exercises will target all major muscle groups (e.g., seated row, chest press, squats, biceps curl). Heart rate monitors (i.e., Fitbits provided to each participant) will be used to encourage PA within target heart rate zones and for self-monitoring. These wearables have been incorporated into several interventions as an intervention tool to increase PA as they provide effective self-monitoring for PA intensity [53, 54]. 

**Table 2 Tab2:** Description of the physical activity intervention

Week	1–2	3–4	5–6	7–8	9–10	11–12	13–18	19–24
Number of sessions/week	3	3	3	3	3	3	2	1
Rating of Perceived Exertion (RPE)	12–13 (aerobic) 12–15 (resistance)	12–13 (aerobic) 12–15 (resistance)	13–14 (aerobic) 12–15 (resistance)	13–14 (aerobic) 12–15 (resistance)	14–15 (aerobic) 12–15 (resistance)	14–15 (aerobic) 12–15 (resistance)	15–16 (aerobic) 12–15 (resistance)	15–16 (aerobic) 12–15 (resistance)
Intensity for aerobic physical activity (% Heart Rate Reserve)	40–59	40–59	50–59	50–59	55–65	55–65	60–70	60–70
Duration of physical activity (min)	10–15 (aerobic) 15–20 (resistance): 1 set of 8–12 reps for 60–80% of one-repetition maximum	15–20 (aerobic) 20–30 (resistance): 2 set of 8–12 reps for 60–80% of one-repetition maximum	15–20 (aerobic) 20–30 (resistance): 2 set of 8–12 reps for 60–80% of one-repetition maximum	20–25 (aerobic) 30 (resistance): 2–3 sets of 8–12 reps for 60–80% of one-repetition maximum	25–30 (aerobic) 30 (resistance): 2–3 sets of 8–12 reps for 60–80% of one-repetition maximum	25–30 (aerobic) 30 (resistance): 2–3 sets of 8–12 reps for 60–80% of one-repetition maximum	25–30 (aerobic) 30 (resistance): 2–3 sets of 8–12 reps for 60–80% of one-repetition maximum	25–30 (aerobic) 30 (resistance): 2–3 sets of 8–12 reps for 60–80% of one-repetition maximum

Following all baseline testing delivered remotely (i.e., physical function), participants will be randomized to one of two groups: PA + BC or PA + EC (attention control). People LWBC in both groups will receive a tapered, home-based program lasting 1 hour for 3 days per week for the first 12 weeks, 2 days per week for week 13–18, and then 1 day per week for week 19–24 (54 sessions total). Qualified exercise professional (QEP)-led, group-based (~ 12 participants per class [55]) PA sessions completed at home via videoconferencing (i.e., Zoom), resistance bands, and an exercise mat will be provided for both groups. Consideration of the different cancer types are addressed through the tailored PA prescriptions and individual counseling sessions. Additional at home/unsupervised sessions will be prescribed, where people LWBC will be asked to complete one PA session on their own for weeks 13–18, and two PA sessions for weeks 19–24 (Fig. 2). Tracking and monitoring tools (i.e., Fitbits, PA logs) will be provided to ensure intensity and duration are met for both groups. A PA manual will be distributed to each participant as an ongoing resource, which will be developed separately for each of the two groups, with the behavioral counseling group containing more content (i.e., theory-based counseling). Sessions will be delivered by QEPs which encompasses graduate students in Kinesiology who are certified trainers with the Canadian Society of Exercise Physiologists (CSEP) or ACSM, as well as Registered Kinesiologists or Physiotherapists with experience working with people LWBC at the University of Toronto site for consistency. Training sessions/manuals will be provided for strict protocol adherence including core delivery components for the counseling sessions, cancer treatment information, PA safety and barriers, and quality control checklists.

*Intervention Group - Physical Activity Group + Behavioral Counseling Group (PA + BC)-*The PA + BC group will receive a behavioral counseling support session with a QEP every two weeks during the intervention period (12 total). The support sessions will be 30–45 min and delivered via Zoom each week in either group or 1:1 format depending on the topic. The videoconference calls will incorporate tailored behavior change content from the M-PAC framework (Table 3; Fig. 2). Of the 12 video-conferencing calls, one session will target reflective processes (instrumental/affective attitudes), five sessions will target behavioral regulation (action planning, coping planning, social support, goal setting, emotion regulation), and four sessions will target reflexive processing (identity, habit). The remaining two sessions are “booster sessions” to revisit topics discussed. The importance of sustaining PA for clinical outcomes (e.g., fatigue) and PA logs will be stressed. At the end of the 6-month intervention, an individualized PA prescription will be provided based on their fitness level (adjusted throughout) to continue achieving the PA goal for the 6-month and 1-year follow-up.

*Attention Control Group ** Physical Activity Program + Exercise Counseling Group (PA + EC)-*The PA + EC group will receive the same frequency of group-based and 1:1 counseling support sessions via Zoom as PA + BC participants. However, the focus will be on PA training principles for proper PA technique, how to monitor intensity, and progress PA safely to achieve the PA guidelines. The support sessions will be 30–45 min and delivered via Zoom each week in either group or 1:1 format depending on the topic (Table 3; Fig. 2).

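### Treatment is partly delivered in groups, and the counseling groups must be arm-specific, yet neither the sample size nor the named model levels include class or counseling group

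*Protocol article*

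**What the plan says.** **Delivery.** Under Study groups, the protocol article puts both arms in exercise sessions led by a qualified exercise professional, at about 12 "participants per class [55]) PA sessions completed at home via videoconferencing", 54 sessions in all. It does not say whether a class holds one arm or both. Counseling in each arm is "delivered via Zoom each week in either group or 1:1 format depending on the topic". Table 3 marks weeks 2, 8, 10, 14, 18 and 22 as group sessions and lists different topics for the two arms. The size of a counseling group is not given.

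**Sample size.** The calculation rests on "a mixed model test with two intervention levels" and one outcome. The result is that "the total sample size of 196 will provide 80% power with alpha 0.05", for a difference of 24 min per day. The target of 236 adds an allowance for 20% attrition and nothing else.

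**Model.** Statistical analysis sets repeated measurements at level 1 and study group at level 2, then adds: "Finally, study group will be nested within study site (level 3". The fixed effects define group as the two trial arms. Class, counseling group and exercise professional appear neither as a level nor among the example covariates.

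**The concern.** People who share a live class or counseling group also share an instructor, a schedule and each other. In this trial the sharing is partly intended: Table 3 lists emotional social support for the week 2 group session and social comparison for the week 18 group session. Some correlation of outcomes within a group is therefore plausible.

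Where a group contains only one arm, between-group variation adds to the variance of the arm comparison. A model that leaves it out uses too small a standard error. Its intervals are then too narrow and its false-positive rate exceeds 5%. A sample size computed as if participants were independent promises more power than the design delivers. A positive result on MVPA could be challenged on this ground, and group membership that was not recorded at the time may be hard to reconstruct.

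**Working it through.** **1. The plan's own figure.** The article gives N = 196, 80% power, alpha 0.05 and 24 min/day, but no SD, so 196 cannot be reproduced from its inputs. Back-solving a two-sided, two-sample t-test with 98 per arm gives d = 0.402, which implies an SD of 24/0.402 ≈ 60 min/day. This d and the two-sided test are assumptions. The target follows as 196 × 1.2 = 235.2, rounded up to the even number 236.

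**2. Formulas.** For arm-specific groups with m evaluable members:
- Design effect: DE = 1 + (m − 1) × ICC
- Effective sample size: N_eff = 196/DE
- Power: noncentral t with noncentrality d × √(N_eff/4), on N_eff − 2 df or on cluster-based df
- Type I error if the group is ignored: 2 × [1 − Φ(1.96/√DE)]
- Interval width relative to the correct width: 1/√DE

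The documents give no ICC. The values 0.01, 0.02 and 0.05 are assumed.

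**3. If exercise classes are arm-specific.** 236/12 ≈ 20 classes, so 196/20 = 9.8 evaluable members per class, and cluster-based df = 20 − 2 = 18. Worked line for ICC 0.02: DE = 1 + 8.8 × 0.02 = 1.176; N_eff = 166.7; noncentrality = 0.402 × √(166.7/4) = 2.595.

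| ICC | DE | N_eff | Power | Power, 18 df | Type I error if ignored | Interval too narrow by |
|---|---|---|---|---|---|---|
| 0.01 | 1.088 | 180 | 77% | 72% | 6.0% | 4% |
| 0.02 | 1.176 | 167 | 73% | 69% | 7.1% | 8% |
| 0.05 | 1.440 | 136 | 64% | 60% | 10.2% | 17% |

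Part of the loss in the 18-df column comes from the few df alone: at ICC 0 the same formula gives about 76%.

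**4. If only the counseling groups are arm-specific.** Their size is unstated; m = 6 is assumed.

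| ICC | DE | N_eff | Power | Type I error if ignored | Interval too narrow by |
|---|---|---|---|---|---|
| 0.01 | 1.05 | 187 | 78% | 5.6% | 2% |
| 0.02 | 1.10 | 178 | 76% | 6.2% | 5% |
| 0.05 | 1.25 | 157 | 71% | 8.0% | 11% |

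**5. Mixed exercise classes.** A simulation with 16 classes of 12, each split evenly between arms and analyzed without class, gave type I errors of 5.0%, 4.8% and 4.3% at the three ICCs. Evenly mixed classes do not themselves inflate the arm contrast.

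**6. Can site or arm stand in for class?** No. About 20 classes lie below site, and the arm-specific counseling groups lie within arm. A fixed arm effect cannot absorb variation between groups inside one arm.

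**The case against.** **The documents do not establish the size.** They give no ICC, and several features could keep it low: individualized prescriptions, half of the counseling delivered 1:1, an outcome measured in free living, and only one supervised class per week in weeks 19–24 before the post-intervention assessment. At ICC 0.01 the loss is two to three points of power before any df correction. This stands as a limit on the size. It does not support an ICC of exactly zero.

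**Separate exercise classes are not stated.** A reader might infer from the two counseling programs that exercise classes are also split by arm. The article does not say so, and the overview figure is not shown. Only the counseling groups are arm-specific by necessity. The tables therefore cover both readings.

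**Harsher numbers are tempting.** A reader might put 12 evaluable people in every class and obtain a type I error of 11.5% at ICC 0.05. But classes of 12 formed from 236 make about 20 classes, which hold about 10 evaluable people each once the number falls to 196. The larger figure mixes randomized and evaluable counts.

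**An analysis plan may add the term.** A separate plan could well name a cohort effect. The article, however, is not silent: it lists its model levels and states a power figure, and neither allows for group delivery.

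**Conclusion.** The point holds in direction and is moderate in size. The arm-specific counseling groups follow from the article's own table, and neither the stated model nor the sample size allows for them. With any positive ICC in such groups, power falls below the stated 80% and the interval for the arm contrast is too narrow.

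Under the assumptions above (d about 0.40, ICC 0.01 to 0.05), power lies between about 78% and 64%, or down to 60% with cluster-based df. The type I error if groups are ignored lies between about 5.6% and 10.2%. The milder ends belong to counseling groups of six alone, the harsher ends to arm-specific exercise classes.

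A reader might conclude that the trial's power claim is void. The documents do not support that: with no SD and no ICC given, the 80% can only be called overstated relative to the independence on which it appears to rest.

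**What to change.** 1. Record the exercise class and counseling group of each participant as sessions run, and state whether exercise classes are separate by arm and how large counseling groups are.
2. Add to the model under Statistical analysis a random effect for the arm-specific group, acting on post-baseline measurements. Groups form after baseline, so a group intercept that is constant over all five time points would largely cancel from the group-by-time contrast and leave its standard error almost uncorrected. Use either a cohort-by-time term or a cohort intercept in a baseline-adjusted model of post-baseline outcomes. Make it partially crossed if people change class, with Satterthwaite or Kenward-Roger df.
3. Restate the power under Sample size over a stated ICC range at the planned 236.

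The cost is an identifier that scheduling should already hold, one more variance component to estimate, and a less favorable stated power. No extra participants are asked for, so the restated power discloses the loss and does not recover it.
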